## Methods: participants, interventions, and outcomes

### Study setting {9}

The study will be conducted at the School of Health and Social Work, University of Hertfordshire, Hatfield, UK.

This is a community study in which participants self-administer their randomized NMES device at home. The Revitive Medic^©^ is intended for use in the home setting without the need for supervision by a clinical professional; the device is widely available for purchase, without requiring a prescription. The device is simple to use with minimal instruction. Participants in the trial will be familiarized with the device at the initial study visit and can contact the investigator to address any queries or concerns.

### Eligibility criteria {10}

Eligible participants will be community-dwelling adults aged > 65 years who have one or more of the following symptoms in one or both legs: aching/pain in the leg, heaviness in the leg, tiredness in the leg, or cramps in the leg at any time in the day or night.

Exclusion criteria will comprise (but not limited to) severe diabetes mellitus with severe diabetic neuropathy; lumbar radiculopathy; restless legs syndrome; active cancer; standard contraindications to NMES treatment such as the presence of an electronic implanted device (e.g., cardiac pacemaker); any significant injury to the leg(s) in the last 6 months; being non-ambulant; inability to communicate in English; and inability to provide informed consent.

### Who will take informed consent? {26a}

Potential study participants will initially be contacted by telephone, at which time the nature of the study will be discussed. It will be explained that full participation in the study depends upon whether they meet eligibility criteria, and participant eligibility for the study will be reviewed. Eligible and willing participants will be entered into the study during the telephone call. After the call participants will be randomized and sent the participant information sheet to review prior to their first study visit. At the first visit, the investigator will review the participant information sheet with the participant and ask if they understand the purpose of and their involvement in the study. Prior to any screening assessments, participants will be asked to voluntarily provide informed consent to participate in the study; if the participant is unsure of any aspect of the study, time will be taken to clarify study details. It will also be explained that the participant can decline the option to participate or can withdraw from the study at any time without needing to give a reason.

### Additional consent provisions for collection and use of participant data and biological specimens {26b}

N/A—participant data will not be used in ancillary studies.

## Interventions

### Explanation for the choice of comparators {6b}

The comparator chosen for the study is “Revitive sham.” This will enable the study to demonstrate how much placebo effect, if any, is achieved with the use of a sham treatment. The comparison between the Revitive sham and the intervention(s) will demonstrate whether the real treatment effects achieved with the active devices are statistically and/or clinically significantly different (i.e., superior) to the placebo effect. To enable successful blinding of the participants, the appearance and all functionalities of the sham device are kept identical to the active devices; however, unlike in the active devices, the stimulation intensity in the Revitive sham is limited to a maximum of 2 (of 99) units. Limiting the intensity level to 2 ensures that a clinically meaningful NMES is not delivered to the tissues, and it is assumed that any potential clinical benefit that may be achieved from this sham application amounts to a placebo effect.

### Intervention description {11a}

#### Revitive Medic© Program 1 and Revitive^®^ Program 2

Revitive, is an approved, commercially available, Class IIa NMES medical device produced by Actegy Limited that stimulates the sensory and motor nerves of the feet and lower legs; the device is CE marked and indicated to manage leg pain and discomfort and/or poor circulation due to inactivity, osteoarthritis, diabetes, peripheral arterial disease, and chronic venous insufficiency. Revitive Medic^©^ Program 1 uses device 3156ADi and a modified device (5520AR) is used for Revitive^®^ Program 2. The difference between these two devices is in the waveform design and the number and order of waveforms. Revitive Medic^©^ Program 1 uses a program of 15 waveforms that runs twice over 30 min; Revitive^®^ Program 2 comprises 6 waveforms delivered in a package of 10 that is run 3 times over 30 min. The electrical stimulation intensity is variable and is controlled and set by the user from 1 to 99 units.

Both devices deliver intermittent, low-frequency impulses through surface electrodes on the footpad to produce (strong) skeletal muscle contraction because of intramuscular nerve branch activation. The devices have an “IsoRocker,” which allows it to gently rock back and forth, creating involuntary ankle movement to replicate heel-toe raises. Both devices are pre-programmed to deliver a series of stimulation patterns that last approximately 60 s each; each pattern is made up of a sequence of stimulation pulses delivered in cycles at frequencies of 20 to 44 Hz and durations of 450–970 μs. Therapeutic levels are dependent on reaching an intensity sufficient to induce motor neurostimulation that causes calf muscle contraction but remains comfortable for the user. The optimal intensity level to induce muscle contraction varies from person to person and may depend on factors including plantar surface skin hydration and comfort.

When first using their device at the baseline assessment visit, baseline sensory and motor thresholds will be established by systematically increasing stimulation intensity in increments of one unit, while the participant provides verbal feedback. The stimulation intensity will be adjusted to the higher limit of what the participant can tolerate; participants will be instructed to use the device at the optimal level identified at their study visit and increase it as necessary to maintain a level that is strong but comfortable for them. Participants will be advised to complete two 30-min sessions each day over the 8-week study period, with sessions being roughly 12 h apart.

#### Revitive sham

Device 3714AN will be used for sham treatment. The only difference between the sham and active devices is in the intensity setting. As explained above, the maximum intensity that a Revitive sham device can deliver is capped at 2 (unlike 99 in the active devices) although the intensity display on the sham device is variable reading up to 99, ensuring that the display is the same as for the active devices. If a participant increases the intensity on the control pad, they will see an increase on the display, but the actual intensity is capped at 2; the increase to a maximum intensity of 2 is achieved in increments that distribute over the full 99-point intensity display scale. For the Revitive sham group, the participant’s familiarization with the device and “Instructions for Use” will be the same as that used for the to active device groups. They will also be advised that the maximum stimulation level may be perceived by some participants but not others and that sensations or feelings often become less noticeable over time. The Revitive sham program runs for 30 min, which is identical to the active devices.

### Criteria for discontinuing or modifying allocated interventions {11b}

N/A—no criteria are specified that warrant discontinuation of the trial intervention.

### Strategies to improve adherence to interventions {11c}

The importance of accumulating 60-min treatment duration per day will be explained to participants at the baseline visit and during device familiarization. Participants will be asked to keep a daily record of treatment sessions undertaken. Participants will be advised that they can contact the investigator at any time with questions relating to study procedures and device use.

### Relevant concomitant care permitted or prohibited during the trial {11d}

During the study, participants will continue with their normal life, activities, medications, and diet with no restrictions.

### Provisions for post-trial care {30}

Any incidental clinical findings identified during study assessments will be reported to the participant, if appropriate, and the participant will be advised to seek medical advice from their general practitioner. Upon completion of the trial, all participants will be offered a new Revitive Medic^©^ Program 1 device, so they can have ongoing access to the trial intervention.

The University of Hertfordshire has provided an agreement to compensate for injury resulting from participation in a sponsored clinical investigation. As such, participants enrolled into the study are covered by indemnity for harm resulting from their participation in the trial.

### Outcomes {12}

The primary endpoint for the study comprises a comparison of change in Canadian Occupational Performance Measure Performance (COPM-P) score from baseline to Week 8 for Revitive Medic^©^ Program 1 versus Revitive sham. COPM-P score is a self-evaluation measure of each participant’s current physical/ occupational performance status.

Secondary endpoints comprise:Change in COPM-P from baseline to week 12, comparing Revitive Medic^©^ Program 1 versus Revitive sham.Change in COPM-P from baseline to weeks 8 and 12 comparing Revitive^®^ Program 2 and Revitive sham.Change in Canadian Occupational Performance Measure Satisfaction (COPM-S) score from baseline to week 8, comparing Revitive Medic^©^ Program 1 versus Revitive sham and Revitive^®^ Program 2 versus Revitive sham. COPM-S score is a self-evaluation measure of each participant’s current satisfaction with their relevant physical/occupational performance.Change in leg pain from baseline to weeks 8 and 12, comparing Revitive Medic^©^ Program 1 versus Revitive sham and Revitive^®^ Program 2 versus Revitive sham; participants will rate leg pain using an 11-point numerical rating scale.Change in blood flow volume and intensity from baseline during device use, comparing Revitive versus Revitive sham.Change in symptom score from baseline to weeks 8 and 12 in terms of overall symptom score and each item (heaviness, tiredness, aching, and cramps), comparing Revitive Medic^©^ Program 1 versus Revitive sham and Revitive^®^ Program 2 versus Revitive sham.

Assessments conducted at the different study visits are presented in Table 1.

**Table 1 Tab1:** Study assessments in the NMES stimulation trial

	**Telephone assessment (≥ week − 1)**	**Baseline assessment** **(week 0)**	**Treatment period**	**Week 8**	**Week 12**
Eligibility	x	x			
Randomization	x				
Informed consent		x			
Demographics		x			
Medical history	x	x	x	x	x
Medications	x	x	x	x	x
Device issue and familiarization		x			
Device usage		x	x	x	
COPM		x		x	x
Symptom (heaviness, aching, tiredness, and cramps) scores		x		x	x
Leg pain		x		x	x
Doppler ultrasound		x		x^a^	
Adverse events		x	x	x	x

^a^For participants with poor quality Doppler data at week 0

Following the 8-week intervention period, participants will return their device to the research team and will be assessed for Week 8 outcome measures. Participants will then return for a repeat assessment of all outcome measures at Week 12, following a 4-week follow-up period without device use. This post-intervention follow-up period is included to assess the short-term maintenance of the treatment effect.

Safety assessment comprises a formal evaluation of all adverse events (AEs), adverse events of special interest (events with a potential causal association to the use of the study device), and serious adverse events (SAE).

### Participant timeline {13}

Participants will be on-study for 12 weeks, with treatment continued for 8 weeks and study assessments conducted at Weeks 0 (baseline), 8 (post-intervention), and 12 (follow-up) as presented in Fig. 1. Participant duration in the trial will continue for 12 weeks.

**Fig. 1 Fig1:**
[figure not shown]
Design of the NMES stimulation trial

Potential participants who express an interest in the study will be contacted by telephone and provided with further information about the study, any questions will be answered and initial screening assessments conducted to inform on eligibility. Once an interested participant is deemed suitable for the study, they will be sent the participant information sheet, randomized, and an appointment will be made to attend the baseline visit; the baseline visit will be arranged for after the participant has had sufficient time to consider the participant information sheet (at least 2 days). Potential participants will be provided with an opportunity to ask questions and request further information about the study at the baseline visit; the participant will also have eligibility criteria checked and provide informed consent. Subsequent procedures will only be initiated once the participant has provided written informed consent.

The participant will undergo baseline assessments and be allocated their study device. Participants will then be instructed as to the correct use of their device and undergo a Doppler assessment of deep leg blood flow volume and intensity both before and during device use. Participants will be sent home with their device to use over the 8-week treatment period.

Participants will return to the study center after 8 weeks (at the end of the treatment period) for study assessments and to return their study device; they will remain on-study for another 4 weeks (follow-up period) during which time they will not use the device. Participants will return to the study center for week 12 assessments, after which they will be considered as having completed the study.

### Sample size {14}

The sample size for the study is 117 participants, with 39 participants in each treatment group.

At the time of protocol development, the anticipated effect of Revitive Medic^©^ Program 1, Revitive^®^ Program 2, and Revitive sham on the primary outcome (COPM-P) was not understood. Multiple publications [27–29] have cited an improvement of 2 points in COPM-P score for an individual participant as a minimally clinically important difference (MCID); a 2-point change in COPM was therefore set as the threshold required for a participant to be considered a responder to the study intervention.

An absolute difference of 30% in the proportion of participants that meet the COPM-P responder definition (improvement of 2 points) between Revitive sham and Revitive Medic^©^ Program 1 or Revitive^®^ Program 2 was considered necessary to demonstrate a clinically meaningful difference for either test device. To control Type I error, a single primary endpoint was chosen namely the difference between Revitive sham and Revitive Medic^©^ Program 1; a comparison of Revitive sham and Revitive^®^ Program 2 is a secondary endpoint. A sequential testing procedure will be employed such that the secondary endpoint can only be formally assessed if the primary endpoint achieves statistical significance (*p* < 0.05).

Basing the sample size calculation on this design, it was determined that 39 participants would be needed in each of the three intervention groups to show an absolute difference of 30% in the proportion of responders between Revitive sham and Revitive Medic^©^ Program 1 or Revitive^®^ Program 2 at 80% power and two-sided 5% significance. For the purposes of the power calculation, the comparison used a Pearson chi-square test at the two-sided significance level (*p* < 0.05).

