### Methods in analysis to handle protocol non-adherence and any statistical methods to handle missing data {20c}

Data from this trial will be summarized and analyzed for the ITT, mITT, and PP populations; analysis of the mITT and PP populations will be considered secondary.The ITT population will include all enrolled and eligible participants who were randomized and used their assigned device at least once. The ITT population will be used to summarize demographic, device compliance, and all efficacy parameters.The mITT will include all enrolled and eligible participants who were randomized and used their assigned device at least once, and for whom the condition being assessed was present at baseline; a separate mITT population will be defined for COPM, symptom score, and leg pain, as these depend on the baseline score for each parameter. In cases where ITT and mITT populations are identical, only the ITT analysis will be presented.The PP population will include participants from the ITT population who were compliant with using their assigned device, defined as missing no more than 28 treatment sessions (minimum 75% compliance). Participants unable to confirm how many treatment sessions they missed will be excluded from the PP population. The PP population will be used to summarize COPM, symptom score, leg pain, and blood volume and intensity data.

Participants who discontinue the study will have data collected up to the point of discontinuation. For participants not assessed at week 8 or 12, the value will be left as missing for calculation and presentation of summary statistics. Participants who do not return their study device at the week 8 visit will be considered as having discontinued the study at this time; this ensures that the potential for continued use of the device after week 8 does not compromise study findings.

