This study has various strengths and some weaknesses. To our knowledge, this is the first study to investigate the effect of foot NMES on the physical function and leg symptoms among community-dwelling older adults with potential underlying issues with leg circulation. The study features a sham control and is adequately statistically powered. The primary outcome measure in the study is “patient-centered” and evaluates physical function at the level that is important to the participants. However, one inherent limitation of the study is that the assessor is not blinded to the study group allocation. The presence of visible muscle contraction with the active NMES devices makes it impossible to blind the assessor.

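### The 80% power quoted for Program 2 ignores the gate (about 70% if both devices have a true 30-point effect), and at the response rates that reproduce 39 per group nothing is left over for losses

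*Protocol article*

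**What the plan says.** All references are to the protocol article.

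- **Size.** Sample size {14}: "The sample size for the study is 117 participants, with 39 participants in each treatment group". The number enrolled is also the number said to be needed: "39 participants would be needed in each of the three intervention groups to show an absolute difference of 30% in the proportion of responders".
- **Power.** The same sentence attaches the power to both devices: "between Revitive sham and Revitive Medic^©^ Program 1 or Revitive^®^ Program 2 at 80% power", with a two-sided 5% level. A Pearson chi-square test on responders (a COPM-P gain of at least 2 points) was used for the calculation.
- **Gate.** The preceding paragraph of that section says that "the secondary endpoint can only be formally assessed if the primary endpoint achieves statistical significance". The calculation is then introduced as resting on this design. The COPM-P part of Statistical methods {20a} confirms the gate: if Program 1 has p > 0.05, Program 2 counts as non-significant and its p-value is descriptive.
- **Sham rate.** Interim analyses {21b} says it came from the 30-participant pilot. The article gives no value.
- **Losses.** Section {20c} provides for discontinuation, treats an unreturned device at week 8 as discontinuation, and says "For participants not assessed at week 8 or 12, the value will be left as missing" in summary statistics. Multiple imputation is used for inference, with non-responder imputation as a sensitivity analysis of responders. Randomization precedes consent ({26a}), and the ITT set requires at least one use of the device.
- **Primary analysis.** Outcomes {12} and {20a} make it the change in COPM-P at week 8, by ANCOVA.
- **Claim.** Discussion: "The study features a sham control and is adequately statistically powered".

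**The concern.** In a gated sequence Program 2 can be declared significant only when two tests succeed, so its power is a joint probability. That must be lower than the power of its own comparison unless Program 1 is almost certain to win. Quoting the same 80% for either device, on a calculation said to rest on the sequential design, gives Program 2 a power that belongs to a different procedure.

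Separately, the enrolled number equals the needed number, although the protocol makes detailed provision for missing outcomes.

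What is at stake is interpretation. A non-significant Program 2 result would be read against 80% when the design offers less, and the unqualified power claim in the Discussion would support that reading. Nothing in the conduct or analysis of the trial changes.

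**Working it through.** **Inputs.** From the article: 39 per group, 1:1:1, a 30-point difference in responders, two-sided 5%, Pearson chi-square, Program 2 tested only after Program 1, no alpha split. Assumed, because not given: the sham responder rate, the loss rate, and equal true effects of 30 points for both devices.

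**1. Reproduce 39.** Pooled-variance formula, with p̄ the mean of the two rates p₁ and p₂:

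n = [1.960·√(2p̄(1−p̄)) + 0.8416·√(p₁(1−p₁) + p₂(1−p₂))]² / (p₂−p₁)²

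At 20% vs 50%, p̄ = 0.35:
- 1.960 × √0.455 = 1.322
- 0.8416 × √0.41 = 0.539
- n = 1.861² / 0.09 = 38.48, so 39

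Power at 39 = Φ[(0.30·√39 − 1.322)/0.640] = Φ(0.861) = 80.5%. Exact binomial enumeration gives 81.3%. The mirror case, 50% vs 80%, gives the same figures. These rates are not unique: 21% vs 51% gives 38.99, also 39.

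Other sham rates, same 30-point difference:

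| Sham rate | Needed per group | Power at 39 |
|---|---|---|
| 10% | 32 | 87.9% |
| 20% or 50% | 39 | 80.5% |
| 25% or 45% | 41 | 78.3% |
| 35% | 43 | 76.5% |

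So 39 is the single-comparison, complete-data number at the rates that yield it. It contains no gate adjustment and no loss allowance there.

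**2. Put the gate in.** Given the sham count s, the two active arms are independent. Let r(s) be the chance that an active arm beats that sham count. Then

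P(both significant) = Σ P(S = s) × r(s)²

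| Sham rate | Single comparison, exact | Program 2 through the gate, exact |
|---|---|---|
| 10% | 89.5% | 82% |
| 20% | 81.3% | 70.5% |
| 35% | 77.8% | 66% |
| 50% | 81.3% | 70.4% |

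Simulation with a shared sham arm (1,000,000 runs) gives 70.6% and 70.4% at sham 20% and 50%. A bivariate normal approximation gives 68.3% and 70.8%. As a sanity check, fully independent tests would give 0.813² = 66%; the shared sham arm raises this to about 70%.

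**3. Put losses in.** Single comparison at sham 20% or 50%, formula of step 1:
- 5% loss: 39 × 0.95 = 37.05 evaluable, power 78.4%
- 10% loss: 39 × 0.90 = 35.1 evaluable, power 76.1%

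Through the gate at 35 per arm, Program 2 has about 65% (simulation). Multiple imputation keeps people in the analysis set but does not restore the outcome information they did not provide.

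**4. The ANCOVA.** No SD or mean difference is given, so its power cannot be computed. For orientation, a two-sample t-test with 39 per group has 80% power at a standardized difference d of about 0.64.

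**The case against.** - **The gate is disclosed and Program 2 is labelled secondary.** Quoting per-comparison power for a secondary contrast is common, and the word joining the two devices can be read as each pair taken alone. This explains the figure, but the section says the calculation rests on the sequential design, and under that design 80% is not Program 2's power.
- **The 70% is conditional.** It assumes both devices have exactly a 30-point effect. A larger Program 1 effect would move it towards the single-comparison figure. This stands, and the assumption must be stated with the number.
- **39 might contain slack.** At a sham rate of 10%, 32 per group suffice and 39 would absorb (39 − 32)/39 = 18% loss. Blocks of 9 hold 3 per arm, so 37 or 38 could have been rounded up to complete blocks (117 = 13 × 9). This too stands. The absence of an allowance is shown only at the rates that reproduce 39, and the full protocol may state the rate and any attrition assumption.
- **The responder test is not the primary analysis.** A continuous analysis normally has more power. If changes are normal with equal SDs, 20% vs 50% responders implies d = 0.84, for which a t-test has 95.6% power at 39 per group and about 92% through the gate. This is illustrative, as the article gives no SD, but it bars any conclusion that the trial as a whole is underpowered.

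A reader might infer that the trial fails to deliver 80% for Program 1, or that the Discussion's power claim should be deleted. The documents support neither. With complete data at the reproducing rates Program 1 has 80.5%; any shortfall needs a loss rate or a different sham rate that the article does not give, and 5% loss costs about two points.

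**Conclusion.** The point holds in a limited form.

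- **Program 2: the stated power is wrong as written.** Under the gate it is about 70% instead of 80%, with no losses, at sham 20% or 50% and equal true effects of 30 points. It is about 66% at an assumed sham rate of 35% and about 82% at 10%.
- **Program 1: conditional only.** The 80% is right for the responder chi-square with complete data at the rates that give 39. It would be about 78% or 76% at an assumed 5% or 10% loss, because no margin is built in at those rates.
- **The Discussion's claim needs qualifying.** It has a stated basis only for the responder comparison of Program 1. The article gives no power for the ANCOVA on change in COPM-P, so power for that analysis is neither confirmed nor refuted.

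**What to change.** Change the text only; add no participants. Trial status reports that recruitment is complete.

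1. In Sample size {14}, state the sham responder rate actually taken from the pilot. It must come from the sponsor's record: 20%, 21% and 50% all fit 39, so it should not be back-calculated.
2. Say that the 80% applies to the single comparison of Program 1 versus sham on responders with complete week 8 data, and give the power with 5% to 10% missing (about 78% to 76% if the rate is 20% or 50%).
3. Replace the 80% for Program 2 with its power under the gate, recalculated at the stated sham rate, naming the assumption of equal 30-point effects (about 70% at sham 20% or 50%).
4. In the Discussion, qualify the power claim as referring to the responder comparison for Program 1. Add that no power was calculated for the ANCOVA on change; the detectable standardized difference of about 0.64 at 80% (39 per group, t-test) can be given for orientation.

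The cost is a few sentences and a less favourable stated figure for Program 2. Design and analysis are unchanged.
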